## Abstract

**Background:**

Music therapy improves neuronal activity and connectivity of healthy persons and patients with clinical symptoms of neurological diseases like Parkinson’s disease, Alzheimer’s disease, and major depression. Despite the plethora of publications that have reported the positive effects of music interventions, little is known about how music improves neuronal activity and connectivity in afflicted patients.

**Methods:**

For patients suffering from Parkinson’s disease (PD), we propose a daily 25-min music-based synchronous finger tapping (SFT) intervention for 8 weeks. Eligible participants with PD are split into two groups: an intervention group and a control arm. In addition, a third cohort of healthy controls will be recruited. Assessment of finger tapping performances, the Unified Parkinson’s Disease Rating Scale (UPDRS), an n-back test, the Montreal Cognitive Assessment (MoCA), as well as oxygenated hemoglobin (HbO_2_), deoxygenated hemoglobin (HbR), and total hemoglobin activation collected by functional near-infrared spectroscopy (fNIRS) are measured at baseline, week 4 (during), week 8 (post), and week 12 (retention) of the study. Data collected from the two PD groups are compared to baseline performances from healthy controls.

**Discussion:**

This exploratory prospective trial study investigates the cortical neuronal activity and therapeutic effects associated with an auditory external cue used to induce automatic and implicit synchronous finger tapping in patients diagnosed with PD. The extent to which the intervention is effective may be dependent on the severity of the disease. The study’s findings are used to inform larger clinical studies for optimization and further exploration of the therapeutic effects of movement-based music therapy on neural activity in neurological diseases.

**Trial registration:**

ClinicalTrials.gov NCT04212897. Registered on December 30, 2019. The participant recruitment and study protocol have received ethical approval from the First Affiliated Hospital of Dalian Medical University. The hospital Protocol Record number is PJ-KY-2019-123. The protocol was named “fNIRS Studies of Music Intervention of Parkinson’s Disease.” The current protocol is version 1.1, revised on September 1, 2020.

## Introduction

### Background and rationale {6a}

Parkinson’s disease (PD) is the second most common neurodegenerative disease that afflicts more than 10 million people worldwide. This disease is characterized by motor disturbances such as resting tremors, bradykinesia, hypokinesia, rigidity, gait disorder, and postural instability [1]. The hallmark tremor and locomotive impairments are caused by the absence of dopamine, typically produced by the substantia nigra (SN). Biologically, Lewy bodies are pathological hallmarks of PD and are hypothesized to be caused by degeneration of midbrain dopaminergic neurons and intraneuronal protein aggregation in surviving neurons. The impairment of the dopaminergic signaling of the SN to key timing brain regions is responsible for maintaining balance and complex muscle movement. The neuronal basis of the perception of timing is understood as neural entrainment, where neuronal activity is synchronized with an external or perceived rhythm (e.g., visual, tactile, or auditory) such that these external cues generate a temporal expectation which allows for the prediction of the next event [2].

Humans unconsciously align motor movement to extrinsic sensory modalities such as visual, tactile, or auditory. Everyday examples of neural entrainments include synchronizing with the footsteps of another person when walking side-by-side or finger and arm movement when listening to an isochronous auditory stimulus of a metronome [3–8]. Music-based therapies are particularly advantageous for treating PD symptoms because it has been shown to be beneficial for improving rigidity and gait, which some pharmaceutical and surgical treatments do not treat effectively [9–12]. A common music-based rehabilitation example is coupling auditory cues, like beats from rhythmic songs or a metronome, with steps [13]. Furthermore, Janzen et al. reports that the effects of priming finger taps to regular beats can also improve gait in PD [14]. These therapies rely on the natural phenomenon of neural entrainment by coupling motor movement to external cues which is also known as sensorimotor coupling.

There are two distinct timing systems associated with sensorimotor coupling. The first hypothesis proposes two paradigms: “automatic timing” and “cognitive controlled timing” [15–17]. The former is believed to be relevant in short intervals of sub-second ranges, where engagement of the cerebellum and basal ganglia are more likely to occur. In comparison, cognitive controlled timing has been hypothesized to be associated with longer timing intervals where conscious, cortical regions such as the prefrontal areas and the supplementary motor area (SMA) are activated [18]. Distinguishing between these two systems is an ongoing endeavor [19].

An alternative to automatic and controlled timing theory, “explicit” and “implicit” timing attempts to describe the neural network involved in producing movement with defined durations (explicitly) in comparison to coordinating or predicting movement in response to a temporally expected external event (implicitly). Explicit timing has been associated with neuronal recruitment in the premotor cortex, basal ganglia, cerebellum, and SMA while implicit is predominantly dependent on the cerebellum [20–22]. PD is diagnosed as a deficit in explicit timing where there are abnormalities in internally generated motor movements [17].

From both schools of thought, PD can be described as deficient in one pathway (cognitive and explicit) and preserved in the other (automatic and implicit). Automatic and implicit timing can be engaged with an external cue (e.g., auditory, tactile, or visual stimuli) to compensate for the loss of cognitive and explicit timing functions. These timing impairments are thought to affect an individual’s internal clock, producing asynchrony measured in temporal integration tasks such as synchronous tapping activities [23]. 2.5 s to 3 s inter-beat intervals were experimentally found to be the upper limit for accurate timekeeping in normal subjects [24]. In comparison, patients with PD generally have difficulty reproducing isochronous intervals; individuals with advanced stages of PD were found to have larger errors in faster beats and shorter interval thresholds [25].

Neuroimaging studies using functional magnetic resonance imaging (fMRI) and rhythmic stimuli have revealed increased neural activity coupling between brain regions associated with auditory processing and movement control such as the premotor cortex, SMA, cerebellum, and the basal ganglia [26, 27]. The beneficial effects from an external pacing stimulus for coupling movement and perceptual timing are thought to be mediated by the cerebello-thalamo-cortical network which has been previously associated with timing [28]. Thus, compensation of a dysfunctional basal ganglia timing system, as seen in a patient with PD’s circuitry, may also be facilitated by the same network. Additional regions that fMRI has revealed to be associated with the observed timing benefits of cueing include the putamen, temporal and parietal cortical areas [29]. Rhythmic auditory stimulation may not merely improve motor control during gait, but more generally maybe used to enhance performance in tasks involving perceptual and motor timing (e.g., finger tapping or duration discrimination).

Complementary to fMRI findings, functional near-infrared spectroscopy (fNIRS) reveals similar cortical neural activity. Mahoney et al. reported significantly higher prefrontal oxygenation in patients with PD during postural control [30]. In another study measuring freezing of gait with fNIRS, significant prefrontal and Brodmann area 10 HbO_2_ (oxygenated hemoglobin) activation only occurred when a turn was anticipated. In comparison, oxygenation did not change during unanticipated turns [31]. Both studies support the hypothesis that explicit motor control (when a turn is anticipated) is impaired while implicit motor control is preserved in patients with PD. In general, most of the research has established that there is an increased HbO_2_ activation in the frontal lobes of patients with PD when walking, particularly the prefrontal cortex and premotor cortices [30, 32, 33].

The use of fNIRS to assess neuronal response and its changes over time with music therapy as an intervention in patients with PD has not been explored yet. We take advantage of fNIRS’s high time resolution, locomotive freedom, and capabilities to detect neural activity in relevant motor control cortices as our primary quantitative measurement for investigating the neurophysiological effects and cortical neural activity changes from coupling motor movements with an external sensory cue. This protocol describes the implementation of an 8-week at-home finger tapping exercise while listening to a commonly known melody for participants with PD as a form of music therapy. In addition to fNIRS, various other assessments are used to determine and to track changes produced from the intervention over a 12-week period.

## Objectives {7}

This study’s primary objective is to investigate how external auditory stimuli coupled with motor movement affect motor synchronization and control in patients with PD to further understand how movement based music therapies or other forms of trained auditory cued movement impact the neural activity in key cortical timing brain regions. To achieve this, we propose the following objectives:
Determine neuronal activation and motor control performance in normal, healthy controls (HC) whose lifestyles and demographic are like those of the PD intervention group and PD control group.Implement an 8-week intervention protocol that utilizes a familiar melody (chosen specifically for the intended population) paired with a simple, at-home finger tapping exercise randomized controlled PD intervention group.Use fNIRS and motor control assessments at four time points collected throughout the study to assess how an external auditory stimulus (over time and repetition) coupled with motor movement affects motor synchronization and control in participants with PD. The collection time points are as follows: the first is collected after consent and allocation while the last 3 are sequentially collected 4-weeks apart from one another (i.e., 4 weeks, 8 weeks, and 12 weeks after the baseline measurement).Investigate the effects of music therapy in PD by comparing the neuronal activity changes and motor control performances between PD control arm and PD experimental group.

### Trial design {8}

The study is a parallel two-group randomized controlled trial comparing motor timing performance of PD participants with and without music-based synchronous finger tapping training. In addition, data collected from a third arm, healthy controls, are assessed and serve as a normal, nonpathological baseline.

## Methods: participants, interventions, and outcomes

### Study setting {9}

The assessments and data collection are to be conducted in the First Affiliated Hospital of Dalian Medical University, China. This trial has received ethical approval from the hospital and is anticipated to be a 2-year study including recruitment, intervention delivery, assessments, and data analysis.

### Eligibility criteria {10}

Potential participants will be recruited from the Neurology Department of the First Affiliated Hospital of Dalian Medical University in China. Only individuals who meet the inclusion criteria will be invited to participate in the study.

There will be two populations participating in this study: one will be patients diagnosed with PD with intervention and the other without. A group of healthy participants will be recruited to serve as healthy controls (HC) that will provide the baseline assessment data to gage the severity of PDs in the patient populations.

The following are the inclusion criteria for participants with PD recruitment:
Aged 40–80 years old, both genders, and right-handed;Clinical diagnosis of idiopathic PD according to the 2015 Movement Disorder Society (MDS) Clinical Diagnostic Criteria for Parkinson’s Disease;Rated as stage I to II on the Hoehn and Yahr scale;Score greater than 21 points on the Montreal Cognitive Assessment (MoCA);Maintain a stable dosing of anti-PD or deep-brain stimulation (DBS) treatment throughout the duration of the study;Able to travel to and participate in the data collection process.

Exclusion criteria for participants with PD recruitments include:
Individuals who do not meet the inclusion criteria;Presence of significant hearing impairments;Extensive previous musical training;A history of any other neurological condition (i.e., Alzheimer’s disease, epilepsy, stroke) or psychiatric disorders (i.e., major depression, psychoses).

The HC group will consist of subjects recruited from hospital staff and students as well as students and faculty members from Dalian University of Technology. In addition, participants’ spouses will also be invited to participate. The HC group must have the following qualities to be included:
Aged 40–80 years older, both genders, and right-handed.

HC will be excluded along the same criteria that was established for the PD recruitment.

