## Interventions

### Explanation for the choice of comparators {6b}

The PD intervention group is compared with the PD control group and a healthy control (HC) group. The PD control group is composed of participants diagnosed with PD and who meet the inclusion criteria. This PD control group is instructed to maintain the participants’ prescribed medication and care documented at the time of baseline assessment including any form of deep brain stimulation, if applicable. Any deviation from what was recorded at the time of taking baseline assessments are recorded during assessments and included when analyzing the data.

The second control group, the HCs, is composed of participants who meet the HC group inclusion criteria. This group predominantly consists of healthy spouses of the PD participants and individuals who share similar demographics to the participants diagnosed with PD. Measurements from the HCs are necessary because they serve as a normal, non-pathological benchmark, which has not been recorded before with this specific demographic and type of study paradigm. Furthermore, since spouses typically have similar lifestyles as their partners the measurements taken may help reduce the uncontrollable deviations due to dietary habits, living conditions, and environmental factors. HCs are asked to continue normal routine and must report any major deviations from baseline assessment routine (e.g., new medication to treat non-neurological illnesses that may affect motor movement or major injuries like head trauma). These deviations are noted for data analysis.

The neuronal activities of generating motor movement or processing a rhythmic external cue each should separately elicit measurable neuronal activation. However, when combined, a sensorimotor integration effect occurs such that motor movement is the result of a rhythmic external cue. Thus, the use of the HC and PD controls is to examine how movement coupled with an external sensory cue (a rhythmic auditory stimulus and in this study, music with rich rhythmic contents) impacts motor synchronization and control in PD.

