## Assignment of interventions: allocation

### Sequence generation {16a}

Participants with PD are sorted into and then randomized into the intervention or control groups in a 1:1 balanced ratio stratified by gender and PD staged I and staged II as determined by the Hoehn and Yahr scale. Allocation into randomized study groups are conducted via a computer-generated random number table and determined during the pre-study procedures during allocation when informed consent and baseline measurements are made. The number generation is facilitated by R3.6.3, a computer random number generator typically used by the Scientific Research Department of the hospital. Participant groups are not known to clinical investigators, site personnel, nor data analyzers.

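### The plan describes the healthy-control source in two different ways and has no rule aligning these controls with the PD groups on age or sex, so the promised likeness is not ensured and the unadjusted PD–healthy comparisons may be confounded

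*Protocol article*

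**What the plan says.** The first objective (Objectives {7}) calls for healthy controls "whose lifestyles and demographic are like those of the PD intervention group and PD control group".

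Two sections say where they come from:
- Eligibility criteria {10}: "The HC group will consist of subjects recruited from hospital staff and students", with university students and faculty named alongside them, and then "In addition, participants’ spouses will also be invited to participate".
- Explanation for the choice of comparators {6b}: "This group predominantly consists of healthy spouses of the PD participants and individuals who share similar demographics to the participants diagnosed with PD". This section rests comparability on couples sharing diet, living conditions and environment.

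The inclusion rule specific to controls is "Aged 40–80 years older, both genders, and right-handed". The PD exclusion criteria (hearing, musical training, neurological and psychiatric history) apply to them as well.

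On balance, Sequence generation {16a} states: "Participants with PD are sorted into and then randomized into the intervention or control groups in a 1:1 balanced ratio stratified by gender", and also by Hoehn and Yahr stage. Concealment mechanism {16b} repeats this for PD participants only. Sample size {14} states an aim of evenly spread age, stage and gender, with no mechanism.

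On analysis, Statistical methods {20a} names a two-sample t test for tapping and neuropsychological measures across the three groups, and a t test for the fNIRS group analysis. Additional analyses {20b} leaves gender and age as factors that might be looked at.

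**The concern.** A healthy benchmark separates disease from other influences only if the two populations are otherwise similar. The plan promises that similarity, but it names two different main sources and gives no procedure that would produce it. The argument from shared households in {6b} applies to spouses only. If recruitment follows {10}, that argument does not cover most of the group.

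Three uses of the healthy group depend on a cross-sectional comparison:
- The Abstract compares both PD groups with healthy baseline performance.
- Eligibility criteria {10} uses the healthy data to gauge PD severity.
- The motor-timing assessment section lets the number and rate of visual cues be changed if patients and healthy subjects do not differ significantly in learning.

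Tapping accuracy, 3-back, MoCA and prefrontal HbO2 can be expected to vary with age, and the cognitive measures with education. A demographic difference could therefore mimic or hide a disease difference in each of these uses. The comparator section adds that no such benchmark has been recorded for this population, so there is no established norm to fall back on.

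**Working it through.** **1. The source texts side by side.** In {10}, staff, students and faculty make up the group and spouses are added. In {6b}, spouses predominate, with demographically similar individuals besides. Informed consent {26a} and Recruitment {15} mention patients and their spouses and no staff or faculty, which fits {6b}. The sections overlap, since staff aged 40–80 could count as similar individuals, but they give the main source differently.

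**2. What aligns controls with PD.** Shared: the 40–80 window, right-handedness and the exclusions. Not shared: stratification, which covers the PD arms only. No matching, quota or stratum ties control age or sex to the PD sample. Education is not addressed. The consent section provides for illiterate participants, while {10} recruits from university faculty, so an education gap is plausible.

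**3. The plan's own figure.** 3 × 70 = 210, and 70 × 0.9 = 63 per group after 10% attrition. The 70 cannot be derived from the text because no effect size or SD is printed. An assumed difference of 0.5 SD (two-sided 0.05, 80% power) gives 63 per group, and 63 / 0.9 = 70. With 63 per group the detectable difference is (1.960 + 0.842) × √(2/63) = 0.50 SD.

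**4. Age.** The documents give no ages or age effects, so both inputs are assumptions. Spurious difference d = (gap in years / 10) × slope in SD per decade. With no disease effect, the rejection probability is Φ(d/SE − 1.96) + Φ(−d/SE − 1.96), where SE = √(2/63) = 0.178.

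| Age gap | 0.1 SD/decade | 0.2 SD/decade | 0.3 SD/decade |
|---|---|---|---|
| 0 years | 0 SD, 5% | 0 SD, 5% | 0 SD, 5% |
| 5 years | 0.05 SD, 5.9% | 0.10 SD, 8.7% | 0.15 SD, 13.4% |
| 10 years | 0.10 SD, 8.7% | 0.20 SD, 20.2% | 0.30 SD, 39.1% |
| 15 years | 0.15 SD, 13.4% | 0.30 SD, 39.1% | 0.45 SD, 71.4% |

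Example: 10 years at 0.3 gives d = 0.30, d/SE = 1.684 and Φ(−0.276) = 0.391. If both PD groups are pooled against controls (126 vs 63), the 10-year row becomes 9.9%, 25.4% and 49.4%.

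**5. Sex.** If PD participants are a share p male and all controls are opposite-sex spouses, the controls are 1 − p male and the gap is p − (1 − p) = 2p − 1. With an assumed sex effect of 0.2–0.5 SD and 63 per group:

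| PD male share | Gap | Spurious difference | Rejection |
|---|---|---|---|
| 50% | 0 points | 0 SD | 5% |
| 55% | 10 points | 0.02–0.05 SD | 5.1–5.9% |
| 60% | 20 points | 0.04–0.10 SD | 5.6–8.7% |
| 65% | 30 points | 0.06–0.15 SD | 6.3–13.4% |

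If only half the controls are spouses and the rest are 50:50, the gap at 60% male falls to 0.60 − (0.5 × 0.40 + 0.5 × 0.50) = 15 points.

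**6. How the two routes combine.** The sex route is largest when controls are nearly all spouses. The age route is largest when they are mostly staff. Both cannot be at full size together.

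**The case against.** The sponsor could fairly answer as follows.

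- **The rule permits a comparable group.** Controls and patients share an age window and exclusions that bear on tapping and cognition, spouses are likely to be close in age, and both {6b} and {14} state an intention of similar or even demographics. This stands. A reader might infer that the recruitment rule cannot deliver similar controls. The documents do not support that: the rule leaves similarity to chance and intention, but does not prevent it.
- **Section {10} lists channels and {6b} describes expected composition.** This softens the conflict but does not remove it. One section says what the group will consist of, with spouses as an extra, and the other makes spouses the main part.
- **The sizes are assumed.** This stands. A 15-year gap is allowed by every stated criterion, but that shows possibility, not likelihood. If the gender aim in {14} is met in the PD groups, the sex gap from spouses is zero.
- **Covariates belong in an analysis plan that is not shown.** Fair as to detail, and missing detail is not the criticism here. The article does name an unadjusted test and makes age and gender optional, and no analysis plan settles which people are recruited.
- **The study is exploratory and its main contrast is randomised.** This stands and limits the reach of the point.

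**Conclusion.** The point holds as a limited one. The two source descriptions differ, and the stated rules do not ensure the demographic likeness that the first objective promises. With the unadjusted t test, cross-sectional PD–healthy comparisons may mix disease with age, sex and education.

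The size is conditional on the mix achieved. It is nil with no demographic gap. Under the assumed slopes, a 10-year age gap alone gives 0.10–0.30 SD and 9–39% false rejection, against a detectable difference of about 0.50 SD. The sex route is small: 6–9% rejection at 60% male even if every control is an opposite-sex spouse. Age is therefore the larger of the two; education was not quantified.

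A reader might go further and infer that the healthy arm is useless or that the trial's efficacy result is compromised. Neither follows. The healthy group also has a within-group secondary outcome under Outcomes {12}, and fixed demographic differences from PD do not bias that change from baseline. The randomised comparison of PD intervention with PD control makes no use of the healthy group and is not confounded by its composition. The change is worth making because it is cheap and cannot be made once control recruitment has closed.

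**What to change.** 1. Make Eligibility criteria {10} and the comparator section {6b} state the same source for healthy controls.
2. Frequency-match the 70 controls to the accruing PD sample by gender and 10-year age band (40–49, 50–59, 60–69, 70–80). Set quotas from PD accrual and close a cell when it is full. Use spouses first, then staff or faculty aged 40–80 for unfilled cells.
3. Drop students as a named source, since the 40-year minimum already excludes most of them.
4. Make age and gender fixed covariates in PD–healthy comparisons instead of optional explorations.

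The cost is recruitment wording, a quota sheet and one sentence on the analysis model. The number of controls, the remaining sources and the sample size are unchanged. The downside is small: control enrolment trails PD accrual and some willing volunteers are declined once a cell is full. Education stays unmatched, so that part of the possible confounding is not removed.

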### Outcomes {12}

The primary outcome measurements of this study are the following:
Improvement or preservation of SFT and continuous finger tapping (CFT) performances from baseline measurements for intervention group.Preserved or improved the Unified Parkinson’s Disease Rating Scale (UPDRS) scores from baselines measurements for intervention group in comparison to control arm.Reduced HbO_2_ levels in prefrontal cortex from baseline measurements for intervention group. Preserved or improved n-back task scores from baseline measurements for intervention group in comparison to control arm.Preserved or improved Montreal Cognitive Assessment (MoCA) scores from baseline measurements for intervention group in comparison to control arm.

Secondary outcome measurements of the study include:
Preserved motor control performances, UPDRS scores, HbO_2_ levels, n-back task scores and MoCA scores from baseline measurements in healthy control group.Preserved or aggravated motor control performances, UPDRS scores, HbO_2_ levels, n-back task scores, and MoCA scores from baseline measurements in PD control group.

These outcomes are determined by analyzing the differences between participants’ pre-, 4-week (during), 8-week (post), and 12-week (retention), neuroimaging, neurophysiological, and SFT performance scores as well as compared with the data from the control arms. Individual and grouped averaged measurements are examined.

Music-based therapies often report beneficial and positive results; however, little is known about how music improves neuronal activity and connectivity in individuals with neurological disease. The primary outcome measurements of this protocol: SFT and CFT performances, HbO2, UPDRS scores, n-back, and MoCA scores act as assessments to quantify the effects of a music-based synchronous finger tapping training in individuals with PD. The trial’s outcomes may be used to enhance current clinical care of patients with PD by supplementing or augmenting current PD treatments with music-based exercises. There are currently no anticipated harmful outcomes because the use of fNIRS has been shown to be clinically safe and feasible. Consequently, this study was determined to be a low-risk intervention by the participating hospital’s Ethics Committee and the Steering Committee.

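### The protocol article sets a MoCA floor for PD participants but none for healthy controls, so the PD-versus-healthy contrast may be attenuated

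*Protocol article*

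**What the plan says.** Eligibility criteria {10} prints two inclusion lists. The PD list includes a cognitive floor: "Score greater than 21 points on the Montreal Cognitive Assessment (MoCA", with the abbreviation's bracket closing there. The HC list is introduced by "The HC group must have the following qualities to be included" and has a single entry: "Aged 40–80 years older, both genders, and right-handed".

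Exclusions for HC are borrowed from the PD list: "HC will be excluded along the same criteria that was established for the PD recruitment". That list has four items: "Individuals who do not meet the inclusion criteria"; significant hearing impairment; extensive musical training; and a history of another neurological condition or a psychiatric disorder. None is a score threshold.

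The HC group is a reference group. Eligibility criteria {10} uses its baseline data to judge how severe PD is in the patients. Explanation for the choice of comparators {6b} says of the HC measurements that "they serve as a normal, non-pathological benchmark", and that most HC will be healthy spouses of PD participants. The abstract plans to compare both PD groups with HC baseline performance. MoCA and n-back are also followed in HC as secondary outcomes (Outcomes {12}).

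**The concern.** The patients' MoCA distribution is cut off below 22 at entry and the HC distribution is not. A spouse aged 76 with a MoCA of 18 and no recorded diagnosis meets the HC criteria as written. A PD candidate with a MoCA of 21 does not meet the PD criteria.

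The planned analysis would not correct for this. The section on finger tapping performances and neuropsychological assessments compares the groups with an unadjusted two-sample t test. The optional further analyses in {20b} name gender, age and PD stage, but not MoCA. Low-scoring HC would pull the reference mean down and make the PD deficit look smaller. This is direct for MoCA. It is plausible but unquantified for n-back, tapping and prefrontal HbO2, to the extent that they depend on cognition.

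**Working it through.** No figure stated in the article is at issue. The check is a reading of the text followed by an illustration of size.

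**Step 1: does the shared exclusion list supply a MoCA floor for HC?** The only candidate is its first item, "Individuals who do not meet the inclusion criteria". It can be read in two ways.

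- *Against the PD inclusion list.* An HC scoring 21 or less is excluded, but so is every HC, because the same list requires a PD diagnosis and Hoehn and Yahr stage I–II. This reading leaves no HC group.
- *Against the HC inclusion list.* This is workable, and it fits {6b}, where the HC group "is composed of participants who meet the HC group inclusion criteria". That list has no MoCA item, so no floor follows.

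The permitted MoCA range at entry is therefore 22–30 for PD. For HC without a relevant diagnosis it is the whole scale up to 30. Any HC at 21 or less scores below every eligible patient at entry.

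**Step 2: how large could the effect be?**

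Inputs from the article:
- PD floor: above 21 (Eligibility criteria {10})
- MoCA maximum: 30 (section MoCA)
- HC planned: 70 (Sample size {14})

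Inputs assumed, because the article gives none: HC MoCA roughly normal, mean 24–27, SD 2–4.

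Formulas, with a continuity correction at 21.5, a = (21.5 − mean)/SD, and φ and Φ the standard normal density and distribution function:
- Share of HC at 21 or less: p = Φ(a)
- Expected number: 70 × p
- Rise in the HC mean if the floor were applied: SD × φ(a)/(1 − Φ(a))

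Worked case, mean 25 and SD 3: a = −3.5/3 = −1.167; p = 0.122; 70 × 0.122 = 8.5; rise = 3 × 0.202/0.878 = 0.69 points.

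Each cell gives p; expected number of 70; rise in the HC mean in points.

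| Assumed HC mean | SD 2 | SD 3 | SD 4 |
|---|---|---|---|
| 24 | 0.106; 7.4; 0.41 | 0.202; 14.2; 1.06 | 0.266; 18.6; 1.79 |
| 25 | 0.040; 2.8; 0.18 | 0.122; 8.5; 0.69 | 0.191; 13.4; 1.34 |
| 26 | 0.012; 0.9; 0.06 | 0.067; 4.7; 0.42 | 0.130; 9.1; 0.97 |
| 27 | 0.003; 0.2; 0.02 | 0.033; 2.3; 0.23 | 0.085; 5.9; 0.68 |

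The normal model ignores the ceiling at 30. A simulation with scores rounded and capped at 30 gave 12.2% and 0.69 points for mean 25, SD 3, and 20.3% and 1.06 points for mean 24, SD 3. The ceiling makes little difference in those cases.

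**Step 3: which comparisons are touched?** The PD-versus-HC difference in mean MoCA would be smaller by the rise shown in the table than if both groups had the same floor. The randomised comparison does not involve HC. The HC secondary outcome, "Preserved motor control performances, UPDRS scores, HbO_2_ levels, n-back task scores and MoCA scores from baseline measurements in healthy control group", is a within-group change from baseline, and an entry floor that differs between PD and HC does not by itself bias it.

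**The case against.** The best counter-argument is that the shared exclusion list opens with failure to meet the inclusion criteria, so the MoCA floor may have been meant to carry over. The wording is loose enough that someone could apply it that way. But as written it either removes all HC or adds nothing, so the sentence needs repair on either view.

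Several limiting points stand:
- Diagnosed Alzheimer's disease, stroke and psychiatric illness are already excluded, so the gap concerns undiagnosed or mild impairment.
- HC also come from hospital and university personnel, among whom low scores may be rare. At an assumed mean of 27 and SD of 2 the effect is negligible.
- An HC group unselected for cognition can be a legitimate choice if the article says so.

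The article condenses a fuller protocol, but this point does not rest on a missing detail. Both inclusion lists and the HC exclusion rule are printed, and they differ.

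A reader might infer two stronger things. The first is that healthy controls would come out worse than patients on average. The documents do not show this. If PD and HC had the same underlying MoCA distribution, the floor alone would make PD look better by the amounts in the table. With a real PD deficit the contrast shrinks and need not reverse. The second is that, because the borrowed exclusion was written for PD patients and speaks of other neurological conditions, a person with parkinsonism could enter as HC. That reading is strained, since the article repeatedly describes these participants as healthy and non-pathological.

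**Conclusion.** The point holds as a fault in the eligibility text with a bounded consequence. No workable reading gives HC a cognitive criterion, so the benchmark group can include people scoring below every eligible patient at entry. The direction is attenuation of the PD-versus-HC contrast, clear for MoCA and possible for n-back, tapping and prefrontal HbO2.

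The size depends wholly on an HC MoCA distribution that the article does not give. On the assumed means and SDs it runs from 0.2 to 18.6 of 70 HC at 21 or less, and from 0.02 to 1.79 points on the HC mean, which is negligible to material. Reversal of the group difference is possible but not shown. The randomised PD intervention versus PD control comparison is unaffected. The change is worth making because the benchmark is a stated purpose of the third group and the correction is cheap.

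**What to change.** 1. Add the PD list's MoCA threshold (above 21) to the HC inclusion list under Eligibility criteria {10}.
2. Apply it at screening, before the HC number is assigned.
3. State that the shared exclusion item on failing the inclusion criteria refers to each group's own inclusion list.
4. If an unselected HC group is intended, say so instead, and adjust PD–HC comparisons for baseline MoCA on outcomes other than MoCA itself.

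**Cost.** MoCA is already given to HC, so no new instrument is needed, but its timing changes. Concealment mechanism {16b} assigns the number once consent is received, while {26a} allows baseline measurements up to 1 week later, so a 10-minute test moves forward to screening. Some candidates would be replaced. Enrolling 70 HC needs about 70/(1 − p) screened: 70/0.997 = 70.2 in the most favourable assumed case, 70/0.878 = 79.7 at mean 25 and SD 3, and 70/0.734 = 95.4 in the least favourable. That is between almost none and about 25 extra.
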